## Abstract

**Background:**

The prevention of type 2 diabetes is a recognised health care priority globally. Within the United Kingdom, there is a lack of research investigating optimal methods of translating diabetes prevention programmes, based on the promotion of a healthy lifestyle, into routine primary care. This study aims to establish the behavioural and clinical effectiveness of a structured educational programme designed to target perceptions and knowledge of diabetes risk and promote a healthily lifestyle, particularly increased walking activity, in a multi-ethnic population at a high risk of developing type 2 diabetes.

**Design:**

Cluster randomised controlled trial undertaken at the level of primary care practices. Follow-up will be conducted at 12, 24 and 36 months. The primary outcome is change in objectively measured ambulatory activity. Secondary outcomes include progression to type 2 diabetes, biochemical variables (including fasting glucose, 2-h glucose, HbA1c and lipids), anthropometric variables, quality of life and depression.

**Methods:**

10 primary care practices will be recruited to the study (5 intervention, 5 control). Within each practice, individuals at high risk of impaired glucose regulation will be identified using an automated version of the Leicester Risk Assessment tool. Individuals scoring within the 90^th^ percentile in each practice will be invited to take part in the study. Practices will be assigned to either the control group (advice leaflet) or the intervention group, in which participants will be invited to attend a 3 hour structured educational programme designed to promote physical activity and a healthy lifestyle. Participants in the intervention practices will also be invited to attend annual group-based maintenance workshops and will receive telephone contact halfway between annual sessions. The study will run from 2010–2014.

**Discussion:**

This study will provide new evidence surrounding the long-term effectiveness of a diabetes prevention programme run within routine primary care in the United Kingdom.

**Trial Registration:**

ClinicalTrials.Gov identifier: *NCT00941954*

## Background

### Overview

The high prevalence of type 2 diabetes mellitus witnessed in the United Kingdom and globally represents one of the greatest public health challenges in the 21^st^ century [1]. Currently, the treatment of diabetes accounts for 7–14% of total health care spending across low to high income regions of the globe and this is projected to increase in the future [2]. This has prompted international and national health care organisations to focus on prevention through targeted recommendations and policy. In the United Kingdom, the NHS health checks programme is aimed at screening all individuals between 40 to 74 years of age for vascular and metabolic disease risk and then treating high risk individuals accordingly [3]. Preventing type 2 diabetes is one of the central aims of this programme. However in the UK, translational research has lagged behind policy change and there has been a lack of diabetes prevention programmes specifically developed for, and evaluated in, routine health care settings. Therefore research programmes are urgently needed to address this need.

### Physical activity and lifestyle in the prevention of type 2 diabetes

Type 2 diabetes is widely considered a lifestyle disease because of its strong links to deleterious lifestyle practices associated with industrialisation. For example, it has been shown that 80–90% of all cases of type 2 diabetes could be prevented through a healthy lifestyle [4,5]. Furthermore, randomised controlled trials across diverse countries and populations have shown that the risk of progressing to type 2 diabetes in high risk populations can be reduced by up to 60% in those receiving lifestyle interventions aimed at promoting moderate- to vigorous-intensity physical activity along with a healthy diet, and weight loss/maintenance [6]. The evidence underpinning the link between physical activity and glucose regulation is particularly compelling because it is supported by the full spectrum of evidence needed to infer causality, from observational research [7], to experimental mechanistic investigation [8], through to randomised controlled trials [6,9]. The general importance of physical activity to health was recently highlighted by the World Health Organization who now rank physical inactivity as the fourth leading cause of premature mortality globally ahead of both obesity and dietary factors [1].

### Translation of research into practice

Lifestyle diabetes programmes with proven effectiveness have used resource-intensive behaviour change strategies involving multiple one-to-one patient contacts which are incompatible with routine healthcare settings given competing health care needs and resource and infrastructure limitations [10]. Therefore, diabetes prevention pathways that are tailored to national and regional health care systems need to be developed and evaluated. Over the last decade, several countries including the United States, Finland, Germany and Australia have met this challenge by developing and evaluating diabetes prevention pathways designed for routine clinical care [11]. Although undertaken in diverse settings, these translational programmes have tended to centre on group-based health promotion programmes aimed at replicating the behavioural goals of gold standard research programmes [11]. However, despite these international advances, there has been limited translational research in the United Kingdom. This has consequently limited the ability of primary care providers to commission robust evidence-based diabetes prevention programmes. In response to this need, we developed and evaluated a brief structured education programme designed to promote increased walking activity and improved glucose regulation in those at a high risk of type 2 diabetes as identified through impaired glucose tolerance. This programmes was found to be highly effective at promoting long-term changes to health behaviour and improvements in glucose regulation [9,12]. The programme was specially tailored to the needs and infrastructure available within primary care; this was achieved through modelling the structure and educational philosophy on an established and nationally available self-management programme for those with diagnosed type 2 diabetes [13]. Therefore the effectiveness of this approach at promoting health behaviour and self-management skills in the prevention of diabetes needs to be established within a routine primary care setting.

### Risk identification

In order to identify those who should be referred into a prevention programme, it is also important to design and evaluate pragmatic methods of identifying those with a high risk of developing type 2 diabetes which can be integrated into routine health care systems. Evaluated diabetes prevention programmes have recruited those with impaired glucose tolerance, commonly referred to as prediabetes, identified through an oral glucose tolerance test (OGTT) [6,11]. This test incurs a substantial burden to both health care professionals and patients and is not routinely conducted or recommended as a method of assessing diabetes risk. Risk scores, either in conjunction with, or instead of, biochemical testing are widely acknowledged as a pragmatic and effective way of identifying risk status and their use is promoted by European level guidance on the prevention of type 2 diabetes [14]. However, there is limited evidence from randomised controlled trials to establish the clinical effectiveness of intervening in those identified by a risk score who are likely to have a lower absolute risk of developing diabetes and represent different characteristics compared to those identified with impaired glucose tolerance.

### Study aim

The aim of the study is to establish whether a pragmatic structured education programme with proven efficacy can promote health behaviour and improve metabolic health in individuals at high risk of type 2 diabetes identified through a validated risk score in primary care.

### Primary objective

· To investigate whether a lifestyle intervention programme, based on a brief pragmatic education programme with minimal ongoing support, can promote sustained long-term increases in physical activity in those identified with a high risk of type 2 diabetes in a primary health care setting.

### Secondary objectives

· To investigate the impact of a lifestyle intervention programme on glucose regulation, progression to type 2 diabetes and conventional cardiovascular risk markers in those identified with a high risk of type 2 diabetes through a validated risk score

· To investigate the impact of a lifestyle intervention programme on measures of quality of life and depression in those with a high risk of type 2 diabetes

· To investigate the natural history of progression to type 2 diabetes over a three year period in high risk individuals identified through risk score technology.

## Methods

### Study design

This study is a clustered randomised controlled trial. Randomization will be conducted at the level of the GP practice by a trained individual who is independent of the study team. Practices were randomised (1:1) to receive control conditions or a structured education programme. A blocked design stratified for practice size was used. The study is designed to adhere to internationally recognized criteria for developing complex interventions [15] and for undertaking and reporting cluster randomised controlled trials [16]. Follow-up will be conducted at 12, 24 and 36 months in order to establish the longer-term effectiveness of the programme and determine the natural history of progression to type 2 diabetes over three years in a high risk UK cohort identified through a risk score in primary care. See Figure 1 for a flow-diagram of the study design. 

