### Sample size

This study was powered to detect a difference in change in ambulatory activity of 2000 steps per day between groups; a difference of this magnitude reflects the primary behaviour change aim of the intervention programme and is consistent with the national physical activity recommendations and the intervention effect observed in the proof of concept study that preceded this trial [9,17]. Previous studies with a follow-up of between 3 to 12 months have reported a standard deviation of change in ambulatory activity of 2500–4000 steps per day in relevant populations [9,18-20]. Therefore, in order to detect a difference of 2000 steps per day between groups, assuming a standard deviation of 4000 steps per day, a power of 90%, a significance of 0.05, a cluster size of 90 (see section titled Participants below) and an intracluster correlation coefficient of 0.02 [21], we require a minimum of 8 clusters. In order to account for potential dropout at the practice level and comply with guidance from the Medical Research Council for minimum cluster numbers [22], 10 GP practice clusters will be recruited to this trial.

This sample size will also have sufficient power to enable clinically significant differences to be detected between groups for change in important secondary outcomes. For example, based on a power of 80%, a significance of 0.05 and a intracluster correlation coefficient of 0.02 [23], the above sample size will allow for a reduction in 2-h glucose of 0.8 mmol/l (based on a standard deviation of 2 mmol/l standard deviation [24]) and a reduction in HbA1c of 0.2% (based on a standard deviation a standard deviation of 0.5% [24,25]) to be detected.

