### Data analysis

The study will be reported according to the internationally recognised CONSORT statement for the reporting of cluster randomised control trials [16]. Those withdrawn from the study due to a diagnosis of type 2 diabetes will have their last observation carried forward. Sensitivity analysis, using multiple imputation, will be used to assess the effect of those missing to follow-up. Random effects regression models, controlled for baseline value and taking into account cluster, will be used to look at the difference between groups in change from baseline in continuous outcome measures after checking for normality and applying transformation techniques where necessary. Extreme outliers (more than 4 standard deviations from the mean) will be removed from the analysis. Survival curves will be calculated to estimate the cumulative incidence of diabetes. The difference in incidence of diabetes in the groups will be tested using the two-sided log-rank test. Statistical significance will be assessed at the 5% level and all analysis will be 2-sided.

Interim analysis will be conducted and reported at 12 months.

In concordance with other physical activity randomised controlled trials undertaken by our group and others [46,47], we will undertake pooled analysis of the study cohort to determine, through regression analysis techniques, the extent to which change in physical activity is associated with change in key biochemical and anthropometric variables; this will help provide additional information quantifying the strength of the association between physical activity and metabolic health in a population with a high risk of type 2 diabetes; any such analysis will be reported with the caveats inherent in undertaking additional pooled cohort analysis within the context of a randomised controlled trial.

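### Practices are randomised within practice-size strata, but the stated model for continuous outcomes does not name the stratum, so its standard errors are conservative if practice size predicts outcome

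*Protocol article*

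**What the plan says.** The Study design section describes the allocation: "Practices were randomised (1:1) to receive control conditions or a structured education programme". It adds: "A blocked design stratified for practice size was used". The number of strata and the cut-points for practice size are not given.

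The Data analysis section states the model for continuous outcomes: "Random effects regression models, controlled for baseline value and taking into account cluster, will be used to look at the difference between groups". It names baseline value and cluster; practice size does not appear. For diabetes incidence the section says: "The difference in incidence of diabetes in the groups will be tested using the two-sided log-rank test". No stratification is mentioned there either.

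The Sample size section claims no gain in precision from the stratification.

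**The concern.** Stratifying by practice size makes the arms similar on that factor. If the factor is related to outcome, the arm difference then varies less over repeated randomisations than it would under simple randomisation. A model without the stratum does not know this. It leaves the between-stratum variation in the practice-level error, so the standard error it reports is larger than the true variability of the estimate.

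With 5 practices per arm the practice-level part matters. On the article's figures, the variance of a practice mean, in units of the individual variance, has a between-practice part of 0.02 and a within-practice part of 0.98/90 = 0.011. At stake are interval width, the actual level of a nominal 5% test, and some power. The direction of the treatment effect and protection against false positives are not at stake.

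**Working it through.** **Inputs from the article.** Sample size section: difference 2000 steps/day, SD 4000, power 90%, significance 0.05, cluster size 90, ICC 0.02, minimum 8 clusters, 10 recruited. Abstract: 5 practices per arm. Data analysis section: two-sided tests at 5%.

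**Assumed, because not given.** Two strata (three and four as sensitivity); a share f of between-practice variance explained by practice size; equal clusters and no loss to follow-up; the SD and ICC apply to the analysed change, with no further gain from baseline adjustment.

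**1. The article's own figure.** Individuals per arm without clustering: 2 × (1.960 + 1.282)² × 4000²/2000² = 84.06. Design effect: 1 + 89 × 0.02 = 2.78. Clusters per arm: 84.06 × 2.78/90 = 2.60. Adding one cluster per arm, as is usual with few clusters, gives 3.60, so 4 per arm and 8 in all. The stated minimum reproduces and does not depend on a stratum term.

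**2. Interval half-width with 5 practices per arm.**

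Half-width = t × 4000 × √[2 × (0.02(1 − f) + 0.98/90)/5]

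- Without the stratum (8 df, t = 2.306, f = 0): SE = 4000 × √(2 × 0.03089/5) = 445; half-width = 1025 steps.
- With a two-level stratum (7 df, t = 2.365):

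| f | Half-width (steps) | Change from 1025 |
|---|---|---|
| 0 | 1051 | +2.5% |
| 0.2 | 981 | −4% |
| 0.4 | 905 | −12% |
| 0.6 | 822 | −20% |

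**3. Break-even.** Adjustment narrows the interval when f exceeds [1 − (t₈/t_df)²] × 0.03089/0.02.

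- Two strata (7 df): (1 − 0.951) × 1.544 = 0.08.
- Three strata (6 df, t = 2.447): (1 − 0.888) × 1.544 = 0.17.

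If f = 0, the widening is 2.365/2.306 = 2.5% with two strata, 2.447/2.306 = 6% with three and 2.571/2.306 = 11% with four (5 df).

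**4. Behaviour of the test.** Simulation of practice means, 100,000 runs per setting, strata of 6 and 4 practices with the arms balanced in each. The two power columns give the model without v with the stratum. The 1500-step effect is assumed.

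| f | Type I error without stratum | Power at 2000 steps | Power at 1500 steps |
|---|---|---|---|
| 0 | 5.0% | 97.5% v 96.9% | 84.0% v 82.5% |
| 0.1 | 4.3% | 97.6% v 97.7% | 83.9% v 84.6% |
| 0.3 | 2.8% | 98.0% v 98.9% | 84.7% v 89.4% |
| 0.5 | 1.7% | 98.4% v 99.6% | 85.3% v 93.8% |

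With the stratum in the model, type I error stays at about 5% throughout. The empirical standard error of the treatment estimate is the same with and without the term: 398 in both at f = 0.3 and about 366 in both at f = 0.5. Only the reported precision differs: the mean half-width at f = 0.3 is 1019 without the stratum and 909 with it.

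**5. The planned secondary effects.** The Sample size section plans 0.8/2 = 0.4 SD for 2-h glucose and 0.2/0.5 = 0.4 SD for HbA1c, also at ICC 0.02. At 0.4 SD, power without v with the stratum is 88.1% v 86.8% at f = 0, 89.0% v 92.8% at f = 0.3 and 89.8% v 96.2% at f = 0.5.

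**The case against.** The strongest objection is that the article condenses a fuller plan. The Data analysis sentence covers all continuous outcomes at once and does not say that its list is complete, so a separate analysis plan could add the stratum. That is fair, and it limits the point to the model as written. But the sentence does state what the model controls for, and the one factor that restricted the randomisation is not in it. The point concerns a stated model, not a missing detail.

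Second, the gain depends on a quantity that the article does not give. Nothing in it links practice size to step counts. Below the break-even share, adjustment makes intervals wider, and with 10 practices each extra stratum level uses one of about 8 degrees of freedom. Leaving the stratum out could therefore be a reasoned choice. This stands, and it is why the size is shown as a range.

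Third, the effect on the primary test is very small. This also stands: the design has ample power at 2000 steps with or without the term.

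A reader might infer that the precision gained by stratifying is lost altogether. It is not: the estimate is equally precise either way, and only the reported uncertainty fails to show it. A reader might also want a fixed effect with reduced degrees of freedom for diabetes incidence. The article specifies a log-rank test there, with no regression model and no practice-level degrees of freedom, so that remedy does not fit.

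**Conclusion.** The point holds as a minor mismatch between design and analysis. Randomisation is stratified by practice size, and the stated continuous-outcome model does not name that factor. If practice size predicts outcome, the reported uncertainty is too large and the test is conservative, with a type I error between 4.3% and 1.7% for 10% to 50% of between-practice variance explained. The power cost is about 1 point or less at 2000 steps. It is about 4 to 6 points at the planned 0.4 SD secondary effects if practice size explains 30% to 50%.

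The documents do not support any claim of bias or excess false positives, and the 8-cluster requirement is unaffected. Nor can adjustment be called free or certain to help: that turns on the number of strata and the variance explained, both assumed here.

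**What to change.** In the random effects models for continuous outcomes, include the practice-size stratum used at randomisation as a fixed effect. Code it with no more levels than the randomisation used, and reduce the practice-level degrees of freedom to match (7 for two strata, 6 for three). State the number of strata. If the stratum is left out on purpose because there are only 10 practices, say so and give the reason before the outcome data are seen, so that the choice cannot follow the results.

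No new data are needed, since the stratum is known from randomisation. The price is one practice-level degree of freedom for each level beyond the first, with the widening shown above if practice size turns out to explain nothing. This change does not extend to the log-rank test.

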**Figure 1 F1:**
[figure not shown]
Design and flowchart for the walking away from type 2 diabetes study.

### Sample size

This study was powered to detect a difference in change in ambulatory activity of 2000 steps per day between groups; a difference of this magnitude reflects the primary behaviour change aim of the intervention programme and is consistent with the national physical activity recommendations and the intervention effect observed in the proof of concept study that preceded this trial [9,17]. Previous studies with a follow-up of between 3 to 12 months have reported a standard deviation of change in ambulatory activity of 2500–4000 steps per day in relevant populations [9,18-20]. Therefore, in order to detect a difference of 2000 steps per day between groups, assuming a standard deviation of 4000 steps per day, a power of 90%, a significance of 0.05, a cluster size of 90 (see section titled Participants below) and an intracluster correlation coefficient of 0.02 [21], we require a minimum of 8 clusters. In order to account for potential dropout at the practice level and comply with guidance from the Medical Research Council for minimum cluster numbers [22], 10 GP practice clusters will be recruited to this trial.

This sample size will also have sufficient power to enable clinically significant differences to be detected between groups for change in important secondary outcomes. For example, based on a power of 80%, a significance of 0.05 and a intracluster correlation coefficient of 0.02 [23], the above sample size will allow for a reduction in 2-h glucose of 0.8 mmol/l (based on a standard deviation of 2 mmol/l standard deviation [24]) and a reduction in HbA1c of 0.2% (based on a standard deviation a standard deviation of 0.5% [24,25]) to be detected.

### Participants

Ten GP practices will be recruited from the Leicestershire region (city and county primary care trusts). Initial contact with each GP practice will be through a letter of invitation to take part. All recruited practices will have an induction visit from the study co-ordinator who will provided training and support for the administrative staff in each of the study sites. Eligible participants will be identified using an automated version of Leicester Risk Assessment tool developed and validated by our group [26]. The automated risk score uses the Morbidity, Information Query and Export Syntax (MIQUEST) programme, designed to extract data from computerized medical records in primary care, to analyse data from six variables (age, sex, ethnicity, BMI, family history of type 2 diabetes, antihypertensive medication status) that are commonly held on local PCT databases. By assigning pre-validated weighting to each variable, individuals are ranked by their risk of undiagnosed impaired glucose regulation or type 2 diabetes with a higher score indicating higher risk. The risk score is calculated as follows:

Risk factor Score = 0.0407 x age

+  0.296 (if male, no change in female)

+ 0.934 (ethnicity, as a practice proportion of south Asians)

+ 0.0859 x BMI

+ 0.440 (if family history of type 2 diabetes, no change otherwise)

+ 0.374 (if on antihypertensive medication, no change otherwise)

In this study, high risk individuals will be classified as those above the 90^th^ percentile of the calculated risk score. Eligible individuals will be sent a letter of invitation, a patient information sheet and stamped addressed envelope by a member of their GP practice. Contacted individuals will be requested to return a reply slip confirming or declining their interest in taking part; those who wish to take part will be contacted by the study team where a baseline consent appointment is arranged. 

Individuals will be excluded from the study if they have an existing diagnosis of type 2 diabetes or are diagnosed with type 2 diabetes at baseline, are taking steroids or are unable to speak English; our experience suggests this approach does not limit recruitment and is able to produce a study population that fully reflects the ethnic makeup of the local population.

Based on a typical GP practice of 4500 adults without known type 2 diabetes, 450 will be eligible for inclusion into the study based on the risk score. Of these we anticipated that 330 (75%) will meet the initial inclusion criteria and be invited to take part in the study. Around 100 (30%) are then expected to consent to take part, of which 10 (10%) will have screen detected type 2 diabetes and therefore excluded at baseline; therefore we anticipate the average cluster size to be 90 individuals (see sample size calculation).

Those diagnosed with diabetes over the course of the study will be informed of their diagnosis and referred back to their health care team for standard care. Progression to type 2 diabetes will be included as a secondary outcome.

Figure 1 shows the flow of the participants through the study.

